### Sample size and eligibility criteria

According to previous studies, the intervention’s minimum effectiveness is 20% [35–37], referring to changes in the PMW construct, behavior, and SAML. Also, because of considering these cultural differences in the intervention’s minimum level of effectiveness, 20% was considered for intervention effectiveness based on the previous study with the same field and approach; taking into account the clustering coefficient of 1.5, alpha 5%, and 90% desired power, we need 54 people per group. Also, considering the 20% probability of attrition in the intervention process, the present study’s sample size was 116, including 58 in the experimental group and 58 in the control group.$$n=\frac{\overline{p}\left(1-\overline{p}\right){\left({Z}_{\beta }+{Z}_{\alpha /2}\right)}^2}{{\left({p}_1-{p}_2\right)}^2}$$

Inclusion criteria were access to the internet and social media apps (such as WhatsApp, Telegram, and Instagram), being a student in one of the universities in the city of Hamadan, and willing to participate in the study. Before participation, students signed written informed consent forms to participate in this study. The Principal Investigator will access consent forms of student participant data that will be nameless. Also, according to the consent form, students were free to withdraw from the study at any time.

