**Methods:**

The present study evaluates an intervention program based on media literacy on substance abuse prevention among students using an integrated social marketing approach. This study aims to complete the SMART model’s sixth and seventh stages, implementing intervention and evaluation. Participants will be students of Hamadan University, Iran. Randomization will occur at the university and school levels, and gathered data will appear at two-time (i.e., pre-test and three months follow-up). Intervention group students will obtain both substance abuse prevention education and substance abuse media literacy (SAML) education between pre-test and 3 months post-test. Students in the delayed intervention will be given this education after study accomplishment; this group will receive their regular courses except for substance abuse prevention and media literacy titles during education intervention. The outcome variables are intentions and substance abuse behavior based on prototype willingness and substance abuse media literacy.

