### Measures

#### Student measures

Students completed questionnaires at 2-time points: a pretest and a 3-month follow-up (Fig. 1). The student questionnaire, containing approximately 100 items, covered substance abuse behavior based on PWM variables outcomes (e.g., attitudes, normative beliefs, behavioral intentions, and willingness), self-reports of the SAML Scale (SAMLS), and process evaluation. In addition, demographic questions comprised age, education level, socioeconomic status, sex, gender, parental education level, marital status, name of university, schools and courses, history of smoking and alcohol consumption, addiction status in parents, close friends, substance abuse status, internet access, amount of social media exposure and use of social media, and motivation to use social media.

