#### Outcome measures

Scales of substance abuse behavior based on PWM included the constructs of attitude, subjective norms, and behavioral willingness, as well as prototype and intents of behavior [32, 39]SAMLS includes 13 questions [29]Process evaluation checklist

Process evaluation included student satisfaction and availability of educational material. The quality of educational material was assessed using a 5-point Likert scale.

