#### Statistical methods

Data were analyzed with SPSS version 23 (SPSS Inc., Chicago, Ill., USA) using analysis of variance (ANOVA), independent *t*-test, and other tests. Generally, if the mean score of variables before the intervention was significantly different between the intervention and control groups, the ANOVA test was used; otherwise, we used an independent *t*-test. The independent samples *t*-test (or the Mann-Whitney *U* test) was used to determine differences in numerical variables between the intervention and control groups. To draw a within-group comparison, we used the paired-sample *t*-test or its nonparametric equivalent, the Wilcoxon test. If necessary, missing data were examined at each time point and handled with an appropriate imputation method. All data of the full protocol and intervention study were potentially shareable after unidentified individuals. All researchers could access the data upon request to the Vice-Chancellor for Research and Technology of Hamadan University of Medical Sciences.

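### The 90% power is calculated for an undefined proportion, while the described outcomes are six scale scores compared as means with none named primary, so the power belongs to no described analysis.

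*Protocol article*

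**What the plan says.** **Sample size and eligibility criteria.** The intervention's "minimum effectiveness is 20" per cent, and this figure is described as "referring to changes in the PMW construct, behavior, and SAML". The printed formula is in p-bar, p1 and p2, so it compares two proportions. The result is given as "alpha 5%, and 90% desired power, we need 54 people per group", "taking into account the clustering coefficient of 1.5". The total is 116, or 58 per group, with 20% attrition assumed. No event, p1, p2, p-bar, standard deviation or mean difference is stated.

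**Abstract, Methods.** "The outcome variables are intentions and substance abuse behavior based on prototype willingness and substance abuse media literacy". None of these is ranked.

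**Outcome measures.** The PWM scales "included the constructs of attitude, subjective norms, and behavioral willingness, as well as prototype and intents of behavior", which makes five constructs. The 13-item SAML scale and a process checklist are listed as well.

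**Statistical methods.** The independent t-test, or the Mann-Whitney test, "was used to determine differences in numerical variables between the intervention and control groups". ANOVA replaces it when baseline means differ significantly. An unspecified category of further tests is also mentioned.

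**Student measures.** The item on the student's own substance abuse status appears in the demographic list: "addiction status in parents, close friends, substance abuse status, internet access".

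**The concern.** A power statement means something only for a particular outcome, effect and test. Here the calculation is for a difference in proportions, while the described analysis compares mean scores. A single 20% figure is also spread over three domains: constructs, behaviour and media literacy. A 20% change in a mean score is not a 20-point difference in a proportion. Converting one to the other needs a standard deviation, or a cut-off that defines an event, and the article gives neither.

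Two things are at stake. First, a reader cannot tell what size of effect the trial can detect on the outcomes it will report. Second, with no outcome ranked, the emphasis could fall after the fact on whichever score shows a difference. The article also does not make clear which collected items measure substance abuse behaviour as an outcome, although the abstract names it as one.

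**Working it through.** **1. The plan's own figure**

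Inputs from the sample-size section: two-sided alpha 5%, power 90%, difference 0.20, clustering factor 1.5.

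- (1.960 + 1.282)² = 10.507.
- Printed formula times 1.5: n = 1.5 × p-bar(1 − p-bar) × 10.507 / 0.04.
- Setting n = 54 gives p-bar(1 − p-bar) = 36 × 0.04 / 10.507 = 0.137, so p-bar = 0.164. That corresponds to about 26.4% against 6.4%.

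The article never states these proportions. Other values of p-bar give very different answers: 36 per group at p-bar 0.10, 83 at 0.30 and 99 at 0.50. So 54 can be reproduced only by solving backwards for an unstated event rate. (The formula is printed without the usual factor 2, and the step from 54 to 58 does not match 20% attrition. Those are separate matters and are not relied on here.)

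**2. What the sample can detect for a mean score**

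This uses a two-sample t-test at two-sided 5% (noncentral t). With clustering, the effective n per arm is n / 1.5: 54 / 1.5 = 36 and 46 / 1.5 = 30.7. The 46 is 58 × 0.8 = 46.4, rounded down.

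| Per arm | Difference for 90% power, no clustering | Same, factor 1.5 | Power at assumed 0.5 SD, no clustering | Same, factor 1.5 |
|---|---|---|---|---|
| 54 | 0.63 SD | 0.77 SD | 73% | 55% |
| 46 | 0.68 SD | 0.84 SD | 66% | 49% |

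The normal approximation (1.960 + 1.282) × √(2/n) gives nearly the same values: 0.62 and 0.76 for 54, 0.68 and 0.83 for 46.

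**3. Effect of baseline adjustment**

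With an assumed correlation of 0.5 between baseline and 3-month score, ANCOVA multiplies the detectable difference by √(1 − 0.5²) = √0.75 = 0.866. For 46 per arm with the 1.5 factor, 0.84 × 0.866 = 0.73 SD. Leaving the clustering factor out would give 0.68 × 0.866 = 0.59 SD, which is too favourable on the protocol's own assumption.

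**4. Several unranked scores**

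Take six scores (five constructs plus SAML) and suppose each is tested at 5% with no true effect. The chance of at least one significant result, for equally correlated test statistics, is:

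- correlation 0: 1 − 0.95⁶ = 26.5%
- correlation 0.5 (simulation): about 21%
- correlation 0.7 (simulation): about 16%

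Scores from one behavioural model in one questionnaire are likely to be correlated, so the independent case is an upper end and not a best guess.

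**The case against.** The strongest reply is that this is a condensed article and that error control is commonly left to an analysis plan that is not shown. The unspecified further tests could include a test of proportions, and substance abuse behaviour could be a binary outcome. These points have force, and they rule out some stronger readings.

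- **That any one of several 5% tests would count as success.** A reader might infer this from the missing ranking. The article gives 5% only in the sample-size paragraph and states no per-test level and no success rule. The 16% to 26% describes a risk, not a rule of the trial.
- **That no binary endpoint will be analysed.** The text supports only that none is named.
- **That actual use is measured only by one demographic item, so a prevention claim must rest on attitudes.** The same list includes smoking and alcohol history. The roughly 100-item questionnaire is not reproduced and is said to cover substance abuse behaviour. The Discussion also intends to look at behavioural effects over the 3 months. Behaviour is poorly defined as an outcome, but it is not shown to be absent.
- **That intention is in effect primary because the abstract mentions it first.** Order of mention is not a ranking, and the same phrase names behaviour alongside it.

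The main point survives all of this. An unseen analysis plan could add multiplicity rules. The mismatch between the sizing endpoint and the described outcomes and tests is nevertheless in the article's own text, and the sample size depends on which outcome is primary.

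**Conclusion.** The point holds. The stated 90% power and 54 per group belong to a comparison of proportions whose event and rates are never given, and they cannot be attached to any analysis the article describes. For a single score, the planned size gives 90% power only for differences between 0.63 SD (54 per arm, clustering ignored) and 0.84 SD (46 per arm, factor 1.5). At an assumed true difference of 0.5 SD, power lies between 73% and 49%.

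These figures rest on a two-sided 5% t-test without baseline adjustment and on the protocol's own factor of 1.5 and 20% loss. The 0.5 SD effect is an assumption, because the article gives no standard deviation or mean difference. The false-positive range also assumes six scores, each tested at 5%, with equal correlations between 0 and 0.7. No corrected sample size can be derived until a primary outcome is chosen.

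**What to change.** Before unblinded analysis:

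1. Name one primary 3-month outcome, chosen and justified by the sponsor. It could be the intention score or a defined substance-use measure.
2. If it is a score, analyse it by baseline-adjusted ANCOVA at two-sided 5%. If it is a binary use measure, define the event, the two assumed proportions and a matching baseline-adjusted analysis.
3. Restate the detectable difference or power for that outcome with the 1.5 clustering factor included. For a score with 46 per arm and an assumed baseline correlation of 0.5, the detectable difference is about 0.73 SD.
4. Treat the remaining scores as secondary with Holm adjustment, or label them supportive only.
5. State which collected items measure substance abuse behaviour as an outcome.

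This changes the wording of the outcome, sample-size and statistics sections. If the primary outcome is among the items already collected, no new data are needed. The cost is a less favourable power statement and, if Holm is used, stricter thresholds for the secondary scores.

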It was anticipated that up to 116 students might take part in the study. This study would have taken place during the 2020–2021 school year. Additionally, program completion and feedback on process evaluation (satisfaction, availability, and quality of material education) would be gathered from the intervention students. The research team used the Standard Protocol Items: Recommendations for Interventional Trials (SPIRIT) checklist to prepare this study [34].

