#### Students

It was anticipated that up to 161 students might be enrolled in this study. Research team members explained the aims of the survey to students and distributed consent forms. Students were eligible to participate if they were members of Hamadan universities and consented to receive SAML and substance abuse prevention education. Students completed consent and permission forms, respectively, before initiating the study.

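### The 20% attrition allowance is miscalculated: 58 per group leaves about 46 after that loss, not the 54 the plan says it needs

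*Protocol article*

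**What the plan says.** All three figures stand together in the protocol article, under Sample size and eligibility criteria. The requirement comes first: "taking into account the clustering coefficient of 1.5, alpha 5%, and 90% desired power, we need 54 people per group". Attrition is brought in next, "considering the 20% probability of attrition in the intervention process", and the result is that the "sample size was 116, including 58 in the experimental group and 58 in the control group". So 58 is presented as 54 enlarged to absorb a 20% loss.

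The total appears in two other places. In the design section, just after Fig. 2, it agrees: "It was anticipated that up to 116 students might take part in the study". Under Processes, Students, it does not: "It was anticipated that up to 161 students might be enrolled in this study".

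**The concern.** Going from 54 to 58 adds four students per group, or 7.4%. An allowance for losing one student in five has to be much larger. If 58 is too small, the trial falls short of its own completer target as soon as its own attrition assumption comes true, and the 90% power is not what the enrolled number delivers.

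This matters because the outcome is measured once after baseline, at the 3-month follow-up, so each student lost before then takes an outcome with them. It is also the only sample size justification in the document. A reader would conclude from it that 116 students keep 90% power after a 20% loss.

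**Working it through.** **Inputs**, all from Sample size and eligibility criteria:
- required per group, before attrition: 54, with the clustering coefficient of 1.5 already included
- attrition: 20%
- stated result: 58 per group, 116 in total
- alpha 5%, two-sided (the printed formula uses Z at alpha/2); power 90%

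**Attempt to reproduce 58**

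| Method | Per group | Total |
|---|---|---|
| Standard inflation, 54/(1 − 0.20) = 67.5 | 68 | 136 |
| Shortcut, 54 × 1.20 = 64.8 | 65 | 130 |
| Stated in the protocol | 58 | 116 |

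Neither method gives 58. The gap is 10 students per group against the standard method and 7 against the shortcut, too large for rounding.

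**Attrition on one arm only.** The attrition phrase could be read as applying to the intervention arm alone. That gives 54 + 68 = 122 or 54 + 65 = 119 in total, with unequal arms. The protocol prints 58 and 58, and a 20% loss from a 58-person intervention arm still leaves 46.4.

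**Back-check from 58**
- Completers at 20% loss: 58 × 0.80 = 46.4 per group; 116 × 0.80 = 92.8 in total, against 2 × 54 = 108 required.
- Shortfall: (54 − 46.4)/54 = 14.1%; counting whole students, (54 − 46)/54 = 14.8%.
- Largest loss that still leaves 54: 1 − 54/58 = 6.9%.

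**Power at 20% loss.** If 54 per group gives exactly 90% power, the standardised effect at that size is 1.960 + 1.2816 = 3.2415. It scales with the square root of the group size, so:
- at 46.4 per group: Φ(3.2415 × √(46.4/54) − 1.960) = 0.852
- at 46 per group: Φ(3.2415 × √(46/54) − 1.960) = 0.849

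Power is about 85%. The type II error rises from 10% to about 15%.

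**The figure of 161.** Split equally, 161 students would leave 161/2 × 0.80 = 64.4 per group, which is above 54. But 161 contradicts the 116 stated twice, and it does not follow from 54 and 20%, which give 136 or 130.

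**The case against.** The strongest counter-argument is that the document does not prove which figure is wrong. A base of 46 gives 46/0.80 = 57.5, which rounds up to 58, and a base of 48 gives 48 × 1.2 = 57.6, which also rounds up to 58. So 58 could be a correct inflation of a smaller base, with 54 the misprint. The 54 cannot be recomputed, because the two proportions behind the 20% difference are not given. This stands as a reason to ask the authors to confirm 54. It does not remove the error: 54 is the requirement the protocol states, and against it 58 is too few.

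A second argument is that the effect is modest and partly guarded against. The protocol plans two contacts with students who withdraw, a gift card at follow-up, and imputation if necessary. The loss of power is indeed only about five percentage points. But retention measures do not make the stated calculation right, and imputing missing follow-up outcomes does not restore the information lost with them.

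A third is that the enrolment target itself is unsettled because of the 161. That is true and should be resolved, but as shown above it does not rescue the calculation.

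**Conclusion.** The concern holds. The protocol's requirement of 54 per group, its 20% attrition and its final 58 per group are incompatible, and no reading of the text reconciles them. At 20% attrition the trial has about 46 completers per group instead of 54, with power of about 85% instead of 90%; 58 per group covers a loss of only 6.9%.

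The shortfall in completers needs nothing beyond the three printed figures, with 54 taken as the requirement. The 85% also assumes that 54 per group does give 90% power and that the clustering coefficient is unchanged by the losses. Whether 54 is itself right is a separate question that the document does not allow to be checked.

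**What to change.** Correct the sentence in Sample size and eligibility criteria in one of these ways:

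1. State that 116 enrolled students (58 per group) tolerate about 7% attrition before the number falls below 54 per group.
2. Keep the 20% assumption and state that it leaves about 46 per group, with about 85% power if 54 gives 90%.
3. Only if recruitment is still open and the sponsor wants 54 completers: change the enrolment figure to 68 per group, 136 in total. Trial status has recruitment ending by the end of May 2021, so option 1 or 2 is the realistic one.

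In the same edit, confirm the 54 with the two proportions it came from, and make the total under Students agree with the rest of the article.

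Options 1 and 2 cost one corrected sentence and a less favourable attrition or power figure, with no change to the design. Option 3 costs 20 more students (136 − 116).

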### Internal review board approval

This paper was taken from a doctoral dissertation in Health Education and Health Promotion. This study was approved by the Research Ethics Committee of Hamadan University of Medical Sciences (code: 9811018459; ID: IR.UMSHA.REC.1398.827).

### Participant characteristics

Subjects were enrolled in this study in 2 plans: university schools and students. It should be noted that Hamadan city is located in the west of Iran. It has 4 state universities, including Bu-Ali Sina University, Hamadan University of Medical Sciences, Hamadan University of Applied Sciences and Technology, and the Hamadan University of Technology. Moreover, it has some non-governmental universities, such as Hamadan Islamic Azad University and Hamadan Payame Noor University [38]. Students were selected by simple random sampling using their ID codes. Thus, students in the cluster in the university, once they are categorized into their stratum, then they are randomized to either the intervention or the control groups.

### Processes

#### Schools of university

First, university permission to conduct the study was obtained. University administrators would access questionnaires for an estimate if demanded. Efforts were made to balance the inclusion of both state and non-state universities, as well as to range in their socio-demographic characteristics. Based on the previous formative research [27] and random sampling of Hamadan universities, 3 universities were expected to participate. Therefore, the number of students in each school or university was obtained by proportional assignment of students to the school (i.e., the school with the largest number of students, the largest number of students assigned). After coordinating with university officials, the research units were rationed. Then, the samples were randomly collected.

#### Students

It was anticipated that up to 161 students might be enrolled in this study. Research team members explained the aims of the survey to students and distributed consent forms. Students were eligible to participate if they were members of Hamadan universities and consented to receive SAML and substance abuse prevention education. Students completed consent and permission forms, respectively, before initiating the study.

#### Protocol

After the Research Ethics Committee of Hamadan University of Medical Sciences approval, the Principal Investigator shared a copy of the revised protocol with all the research team members to ensure awareness of the reconsiderations. The research team will document any unexpected deviations from the protocol. Concerning the Data and Safety Monitoring Plan, the Research Ethics Committee of Hamadan University of Medical Sciences will be informed of any updates and modifications.

#### Randomization

Randomization was performed using a stratified random sampling procedure; individuals were assigned to 2 intervention and control groups. Randomization was performed after students signed informed consent, as well as the approval of universities to perform the study.

#### The intervention description

As noted based on the previous formative-mixed methods research, materials, the content of interventions, and the type of delivery channel to participants (which was based on audience tendencies) were identified and developed, and interventional education was developed by an interdisciplinary group consisting of specialists in psychology, media research, web site development, multimedia design, and health education and promotion.

SAML and preventive substance abuse educations were web-based and comprehensive education programs for university students, providing appropriate and medically accurate information about substance abuse using a media literacy education approach. It should be noted that this interventional education would be web-based because of the COVID-19 pandemic to comply with health protocols in Iran. Some advantages of this approach are as follows: Because of the COVID-19 pandemic and social-distancing measures in Iran, it is not clear when universities can return to normal education situations and face-to-face educational interventions. Thus, a web-based approach to delivering education interventions in person was selected. Also, this approach allows for a fully interactive environment or 2-way forms of communication, often between individuals who know each other (e.g., friends) and may have a strong influence on behavior. Moreover, the health of participants is valuable and important for all researchers.

Also, the web-based channel was based on audience preferences and provided more access to materials for interventions. This channel is more flexible, and students can access it at all times and any place, and any individual concerning personal conditions can educate and use educational materials.

Some disadvantages of this approach are as follows: access to comprehensive materials and support can be difficult, and this approach requires additional training before starting educational interventions.

The pairing of preventive substance abuse information and SAML education allows the program to teach students critically thinking about media messages related to substance abuse specifically marijuana and substance abuse behaviors. It mostly teaches them what lifestyles, values, and points of view are represented in or omitted from media messages about substance abuse, such as identification and the possible implications of actual consumption of drugs, including simulating an actor, having instant excitement, believing in the non-addictive nature of advertised substance, and having ideal moods and herbal and not harmful effects.

Education consisted of 5 web-based education sessions about substance abuse prevention and SAML. Each session included 40–45 min of training with the question-and-answer methods. Group discussions (chat rooms) were held with multimedia tools and reminder messages, such as the first educational session to familiarize students with drugs, especially marijuana and substance abuse behavior consequences. The second session aimed to educate students on SAML skills, critical thinking, and media consumption regime. The third session aimed at familiarizing students with interpersonal skills and self-awareness, and the fourth session taught students how to say no and how to solve problems. The fifth session corrected students’ beliefs and attitudes toward substance abuse using the mentioned web-based teaching methods and materials—each containing group discussion in chat rooms. The intervention group received lessons between completing the pretest and follow-up (Fig. 3). The website contained an educator dashboard for educators. They will be one of the research teams to enroll the students in the program and group discussions, including chat rooms, to correct their beliefs about drugs. Educators were also allowed to use web-based education programs in order to make education programs more accessible to students. All educators were requested to review all of the materials.

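### The intervention arm is taught partly in group chat rooms, but the named between-arm tests treat students as independent; if rooms are fixed and scores correlate within them, type I error exceeds 5%

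*Protocol article*

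**What the plan says.** **Delivery.** The intervention description sets out five web-based sessions of 40 to 45 minutes and states that "Group discussions (chat rooms) were held with multimedia tools and reminder messages". The same section gives two-way communication, often between people who know each other, as an advantage of the web channel because it may influence behaviour. The section on the delayed-intervention group says that controls had lessons and educators too, but that substance-abuse and media-literacy topics were withheld until the 3-month data had been collected.

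**Analysis.** Under Statistical methods, the independent t-test or Mann-Whitney test "was used to determine differences in numerical variables between the intervention and control groups". ANOVA is used where baseline means differ significantly. Unspecified other tests are mentioned. No named test has a cluster term.

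**Sample size.** The calculation is made "taking into account the clustering coefficient of 1.5", and with "alpha 5%, and 90% desired power, we need 54 people per group". The level of that clustering is not named.

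**Unit of randomisation.** The Randomization section says that "individuals were assigned to 2 intervention and control groups". The Abstract places randomisation at university and school level.

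**The concern.** The outcomes are attitudes, norms, willingness, intention and media literacy. Group discussion is meant to move exactly these. Students who talk in the same room under the same educator may therefore end up more alike than students from different rooms. A t-test, rank test or ANOVA on individual students counts each one as a full independent observation. With positive within-room correlation, the variance of the intervention mean is larger than the test assumes, so the interval is too narrow and the error leans towards declaring an effect.

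Randomising individuals does not by itself prevent this, because the grouping arises after allocation. The factor of 1.5 does not cure it either: a larger sample protects power, but the standard error used in the test stays the same.

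**Working it through.** **1. The plan's own figure.** The inputs, all from the sample size section, are two-sided alpha 5%, power 90%, a difference of 20% ("20% was considered for intervention effectiveness based on the previous study") and clustering 1.5. The printed formula is n = p̄(1 − p̄)(Zβ + Zα/2)² / (p1 − p2)², with (1.282 + 1.960)² = 10.507.
- p1, p2 and p̄ are not stated, so 54 cannot be derived directly. Solving backwards, 1.5 × p̄(1 − p̄) × 10.507 / 0.04 = 54 requires p̄ ≈ 0.164. Without the 1.5, n would be 36.
- So 54 is compatible with a design effect of 1.5 applied to the sample size. Nothing shows what kind of cluster it stands for.
- The final size is "58 in the experimental group and 58 in the control group". The attrition step does not follow from the stated 20% (54/0.80 = 67.5, so 68), but that is a separate matter. I use 58 per arm below.

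**2. Effect of clustering in one arm.** Take k equal rooms of m = 58/k students in the intervention arm and independent controls. k and the ICC are assumptions.
- Design effect in the intervention arm: DE = 1 + (m − 1) × ICC.
- True SE / t-test SE: r = √((DE + 1)/2).
- Actual two-sided error of the nominal 5% test: 2 × (1 − Φ(1.96/r)).

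Example, 5 rooms at ICC 0.05: m = 11.6; DE = 1 + 10.6 × 0.05 = 1.53; r = √(2.53/2) = 1.125; 1.96/1.125 = 1.743; error = 8.1%.

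| Rooms | m | ICC | DE | r | Error, formula | Error, simulated |
|---|---|---|---|---|---|---|
| 10 | 5.8 | 0.02 | 1.10 | 1.024 | 5.6% | 5.5% |
| 10 | 5.8 | 0.05 | 1.24 | 1.058 | 6.4% | 6.7% |
| 10 | 5.8 | 0.10 | 1.48 | 1.114 | 7.8% | 7.4% |
| 5 | 11.6 | 0.02 | 1.21 | 1.052 | 6.2% | 6.1% |
| 5 | 11.6 | 0.05 | 1.53 | 1.125 | 8.1% | 8.3% |
| 5 | 11.6 | 0.10 | 2.06 | 1.237 | 11.3% | 11.3% |
| 3 | 19.3 | 0.02 | 1.37 | 1.088 | 7.2% | 7.2% |
| 3 | 19.3 | 0.05 | 1.92 | 1.208 | 10.5% | 10.2% |
| 3 | 19.3 | 0.10 | 2.83 | 1.384 | 15.7% | 16.0% |
| 2 | 29 | 0.02 | 1.56 | 1.131 | 8.3% | 8.0% |
| 2 | 29 | 0.05 | 2.40 | 1.304 | 13.3% | 13.4% |
| 2 | 29 | 0.10 | 3.80 | 1.549 | 20.6% | 21.2% |

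The simulated column is the rejection rate of the independent t-test in 20,000 trials per setting, 58 v 58, with zero average effect and real differences between rooms. At ICC 0 the rate stays at 5%.

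**3. Illustration with the plan's factor.** If a design effect of 1.5 applied to the intervention arm only, r = √(2.5/2) = 1.118 and the error is 8.0%.

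**4. Price of the corrected analysis at ICC 0.05.** Approximate Satterthwaite degrees of freedom are (DE + 1)² / (DE²/(k − 1) + 1/57). Relative interval width is r × t(0.975, df) / 1.981, where 1.981 is the t value on 114 degrees of freedom.
- 10 rooms: df 26.6, t 2.053; 1.058 × 2.053/1.981 = 1.10.
- 5 rooms: df 10.6, t 2.211; 1.125 × 2.211/1.981 = 1.26.
- 3 rooms: df 4.6, t 2.642; 1.208 × 2.642/1.981 = 1.61.

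**The case against.** - **Room structure is not documented.** The article gives no number of rooms, no number of educators and no assignment rule. It says students could reach the material at any time and that online lessons were open to all. One common room, or rooms that changed between sessions, fits the text equally well. This stands, so the conclusion has to be conditional.
- **The 1.5 is not tied to chat rooms.** A reader might infer that the authors expected chat-room dependence and then ignored it. The text does not support that: the groupings it names when describing sampling are universities and schools. What remains is narrower: clustering is allowed for somewhere in the sample size, and none of the named between-arm tests accounts for it at any level.
- **Controls were not untouched.** They had lessons and educators without the substance topics. Treating each control as a cluster of one is an assumption.
- **The excess is not universal.** A reader might infer that false positives exceed 5% in any case. With many small rooms and a low ICC the excess is slight. If students are randomised individually and the programme alters nobody's score, rooms formed afterwards create no excess and the error stays near 5%. The inflation concerns a zero average effect with genuine differences between rooms.
- **The article is condensed.** It mentions other tests, and an analysis plan may exist. This tempers the point. It does not remove it, because the between-arm tests are named and assume independence.

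**Conclusion.** The point holds conditionally. The documents establish that group discussion was part of the intervention sessions, that controls did not receive the programme before follow-up, and that the named between-arm tests assume independent students. They do not establish fixed rooms, their number, or the ICC.

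Given fixed rooms and positive within-room correlation, the direction is certain: the standard error is too small and the test of a zero average effect is anti-conservative. On the assumed range the error runs from about 5.5% (10 rooms, ICC 0.02) through about 8% (5 rooms, ICC 0.05, or a design effect of 1.5 in one arm) to more than 10% (2 or 3 rooms at ICC 0.05 or above). The calculations are for the t-test.

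Everything here also presumes individual randomisation. If the Abstract's account governs, both arms are clustered and a one-arm room effect is the wrong model.

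**What to change.** 1. Reconcile the Abstract with the Randomization section on the unit of randomisation. If universities or schools are randomised, the analysis must account for clustering at that level in both arms, and the steps below do not apply.
2. If individuals are randomised, state the number and size of rooms and the number of educators. Record each intervention student's room and educator, or recover them from website records where possible.
3. Beside the simple comparison, report a partially nested linear mixed model for the 3-month score. Include baseline score and university as covariates, a random room effect in the intervention arm, and Satterthwaite or Kenward-Roger degrees of freedom. Treat controls as singletons only if their own lessons were not grouped.
4. If there was one common room, or membership changed between sessions, say that the group effect cannot be separated from the programme effect and give this as a limitation.

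**Cost.** Data collection grows by two variables, and mixed models are available in SPSS. The statistical price is real: at ICC 0.05, intervals are about 10% wider with 10 rooms, 26% with 5 and 61% with 3. It is highest where rooms are few, which is also where the simple test is least reliable.
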